**Table 1. Timing of data collection contacts and FECH contacts (if applicable)\***

| Contact purpose                                                                   | Time Post Discharge | Questionnaires used, also: demographics (DD); services used (SU, includes RACF admission); qualitative interview ( QI) |
|------------------------------------------------------------------------------------------|----------------------------|-------------------------------------------------------------------------------------------------------------------------------|
| T1 (baseline) data collection**                                                          | 1-4 days                   | DD, AQoL-8D, CGI, PCS, FACQ, SAS, BADLI, SU                                                                                   |
| FECH Contacts 1-4: one week, 2 weeks, 1 month, and 2 months post-discharge |                            |                                                                                                                               |
| T2 data collection                                                                       | 3 months                   | AQoL-8D, PCS, FACQ, SAS, BADLI, SU                                                                                            |
| FECH Contact 5: 4 months post discharge                                    |                            |                                                                                                                               |
| FECH Contact 6: 6 months post discharge                                    |                            |                                                                                                                               |
| T3 data collection                                                                       | 6 months***                | AQoL-8D, CGI, PCS, FACQ, SAS, BADLI, SU, QI (subset)                                                                          |
| T4 data collection                                                                       | 12 months                  | AQoL-8D, CGI, PCS, FACQ, SAS, BADLI, SU, QI (subset)                                                                          |

\* Tool name abbreviations shown in text above. \*\*Followed by random assignment to group.

\*\*\*After FECH Contact 6 if in intervention group.

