### *Data Linkage*

Linked administrative health data from each State's data linkage services will be used to capture health service use for all carers and care recipients for 12 months prior (pre-baseline) and at least 12 months post recruitment (follow up), including: Emergency Department (ED) attendance, admission to hospital, length of stay, and use of ambulance services. Use of services covered by the Medicare Benefit Scheme (MBS) (eg, GP visits) and Pharmaceutical Benefits Scheme (PBS) (medication usage) will be captured via Commonwealth departments. MBS/PBS data will be elicited via the DHS (now Services Australia) for patients providing written informed consent to access these data.

Pre-baseline resource use data will provide additional baseline variables to control for potential confounding or effect modification in the effectiveness and cost effectiveness analyses. The difference between pre- and post-baseline use of health services will be used to measure changes in carers' and care recipients' levels of utilisation and cost of health services for participants in both study arms.

Charlson's Co-morbidity Index (43) will be referred to to determine comorbidity at recruitment for carers and care recipients, using hospital data (when available) supplemented by carer reports. Additional information provided by carers about health and care services received by patients and carers will clarify services used and obtain a more comprehensive picture.

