**Preparation for economic analyses.** As noted above, carer health state utilities will be captured at baseline and for the previous 12 months for all carer participants who meet the inclusion criteria, and at 3, 6, and 12 months post recruitment. The AQoL-8D (13, 14) utility algorithm weighted for the Australian population will be used to derive an overall index of the health state utility at each time point. The QALY profile for each carer will be calculated using area under the curve methods.

**Cost utility and cost effectiveness analyses.** These analyses will be led by CI [name], a highly experienced health economist and will evaluate all outcomes that show a significant difference across the arms of the trial. Cost effectiveness of the intervention will be measured using the

framework of a within trial cost utility analysis. An incremental cost-utility analysis will be undertaken to compare the mean incremental cost and quality adjusted life year (QALY) profiles for each group according to intervention status. We will also estimate cost effectiveness utilising measurement of the change in other secondary outcomes where a significant difference is observed between the intervention and control groups. Confidence intervals will be presented around the incremental cost effectiveness ratios (ICER), and cost effectiveness acceptability curves for varying threshold values of cost effectiveness will be presented. A 12-month time horizon will be used and a health system perspective using within trial probabilities and costs will be undertaken. Assessment of the sensitivity of the results obtained to variation in measured effectiveness, health care resource use, intervention and usual care unit costs and participant subgroups will be undertaken using one-way and probabilistic sensitivity analysis, as per best practice guidelines (51).

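### The protocol claims carer utilities for a pre-baseline year that no visit collects, and its QALY comparison does not name baseline utility as a covariate, which costs precision

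*Protocol*

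**What the plan says.** In the protocol's Statistical Analysis section, the paragraph on preparation for economic analyses refers back to earlier text and states that "carer health state utilities will be captured at baseline and for the previous 12 months for all carer participants". The follow-up utilities in that sentence are those at 3, 6 and 12 months. On the QALY itself the paragraph says: "The QALY profile for each carer will be calculated using area under the curve methods". The next paragraph plans a within-trial cost-utility analysis that will "compare the mean incremental cost and quality adjusted life year (QALY) profiles for each group according to intervention status". On its length the protocol says: "A 12-month time horizon will be used".

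Three other places bear on this:

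- **Table 1.** The T1 contact, 1-4 days after discharge, lists "DD, AQoL-8D, CGI, PCS, FACQ, SAS, BADLI, SU". AQoL-8D appears again at 3, 6 and 12 months, and nowhere before T1.
- **Data Linkage.** "Linked administrative health data from each State's data linkage services will be used to capture health service use", and this covers the 12 months before baseline. The section adds that pre-baseline resource use will supply further baseline variables for confounder control in both the effectiveness and the cost-effectiveness analyses.
- **Statistical Analysis, effectiveness model.** Baseline differences enter the mixed model for AQoL-8D change as covariates only if they are seen.

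Hypothesis 2 (Aims and Hypothesis) is judged on an incremental cost-effectiveness ratio (ICER) below AUD 50,000 per QALY for carers.

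**The concern.** There are two linked problems.

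First, the protocol describes a year of carer utility data that no procedure produces. The back reference leads to nothing: no earlier section mentions utilities before T1. An analysis plan cannot supply data that are never collected, so the text has to be corrected in the protocol.

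Second, the protocol fixes how the QALY is built (area under the curve) and which contrast is made (group means), and it names pre-baseline resource use for adjustment in the economic analysis. It does not name T1 utility. A QALY is a level, not a change, so baseline is not subtracted as it is in the primary outcome. A chance difference in T1 utility enters the QALY directly as the first point of the curve, and indirectly because carers with higher utility at T1 tend to have higher utility later. The precision of the ICER and of the acceptability curve for Hypothesis 2 depends on whether this is removed.

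**Working it through.** **Stated sample size.** For an effect size of 0.22, 80% power and two-sided 5%: n per arm = 2 × (1.960 + 0.842)² / 0.22² ≈ 324.3, rounded up to 325. The protocol has 324 (Power Calculations), where power is 0.7996. It therefore reproduces, and 324 per arm is used below to size a chance imbalance. The protocol gives no QALY figure to reproduce.

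**Inputs not in the protocol (assumptions).** Equal utility SD at all visits; one common correlation r between visits, range 0.5-0.8; T1 treated as time 0. Ratios below do not depend on the SD. Where a value in utility units is shown, SD = 0.20.

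**Step 1: weights.** The trapezoid rule at 0, 0.25, 0.5 and 1 year gives
- T1: 0.25/2 = 0.125
- 3 months: 0.25/2 + 0.25/2 = 0.25
- 6 months: 0.25/2 + 0.5/2 = 0.375
- 12 months: 0.5/2 = 0.25

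These sum to 1. All four come from visits in Table 1, so the 12-month QALY needs no pre-baseline utility.

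**Step 2: share of a baseline difference carried into the QALY.** The slope of QALY on T1 utility is b = 0.125 + 0.875r.

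**Step 3: variance, in units of SD².** The squared weights sum to 0.28125. Unadjusted variance V = r + (1 − r) × 0.28125. Adjusted for T1 utility it is V − b².

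**Step 4: size against the planned effect.** The SE of the T1 difference is SD × √(2/324) = 0.0786 SD. A 0.22 SD effect held at 3, 6 and 12 months is worth 0.875 × 0.22 = 0.1925 SD in QALYs. The ratio is 0.0786b / 0.1925.

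| r | b | V | V − b² | Variance ratio | One-SE imbalance / planned effect |
|---|---|---|---|---|---|
| 0.5 | 0.5625 | 0.6406 | 0.3242 | 2.0 | 23% |
| 0.7 | 0.7375 | 0.7844 | 0.2405 | 3.3 | 30% |
| 0.8 | 0.8250 | 0.8563 | 0.1756 | 4.9 | 34% |

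**In utility units** (SD 0.20, r = 0.7): the SE of the T1 difference is 0.0157; the amount carried is 0.7375 × 0.0157 = 0.0116 QALY; the planned effect is 0.1925 × 0.20 = 0.0385 QALY. The SE of the QALY difference is 0.0139 unadjusted and 0.0077 adjusted.

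**Sensitivity to n.** If all randomised carers are kept through multiple imputation, about 925/2 ≈ 462 per arm have T1 data. The one-SE imbalance falls by the factor √(324/462) = 0.84, so 23-34% becomes about 19-28%.

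**The case against.** Three stronger readings are tempting, and the protocol supports none of them.

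- **A reader might infer that the QALY includes a pre-baseline year.** The disputed words stand in a sentence about data capture, not in the area-under-the-curve sentence. The analysis is within-trial with a 12-month horizon, and Methodological Approach ties the one-year follow-up to QALY determination. The phrase looks like a carry-over from the service-use look-back. Nothing suggests filling in that year from T1.
- **A reader might infer that the protocol rules out baseline correction.** It does not. Comparing group means names the contrast without excluding covariates, and Data Linkage foresees baseline control in the cost-effectiveness analysis. A health economics or statistical analysis plan that is not shown may already name T1 utility.
- **A reader might infer that chance imbalance is booked as a gain.** Under randomisation the unadjusted difference is unbiased and the error falls either way. The planned intervals for the ICER, the acceptability curves and the probabilistic sensitivity analysis would carry that extra uncertainty.

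These arguments limit the point but do not remove it. Resource use is not utility. The conditional rule belongs to the effectiveness model. Wide intervals that report avoidable noise honestly are still wider than they need to be.

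**Conclusion.** The contradiction over pre-baseline utilities is certain: the economic section, Table 1 and Data Linkage must be reconciled. It is a drafting error that does not affect the 12-month QALY.

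The covariate point holds as one of efficiency. With r between 0.5 and 0.8, about 56-83% of a chance T1 difference reaches the unadjusted QALY difference, mostly through the correlation with later visits and not through the 0.125 weight. The standard error is about 1.4 to 2.2 times what the same data allow (√2.0 to √4.9). The ranges rest on the assumed common correlation and equal SDs, since the protocol gives neither, and on complete profiles. If an unseen analysis plan already adjusts for T1 utility, only the wording correction remains.

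**What to change.** 1. In the paragraph on preparation for economic analyses, remove the pre-baseline year from the utility sentence and state that AQoL-8D utilities are captured at T1, 3, 6 and 12 months. Keep the 12-month look-back for service use under Data Linkage.
2. Define the carer QALY as the trapezoidal area over those four points within the 12-month horizon.
3. Estimate the incremental QALY, and hence the ICER and acceptability curve, by regressing each carer's QALY on arm with T1 AQoL-8D utility as a prespecified covariate, whether or not a baseline difference is seen. The planned resource-use covariates can stay alongside it.

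The cost is a corrected sentence and one regression term. T1 utility is already collected, so no visit, questionnaire or sample size changes.

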### *Qualitative Analysis*

Thematic data analysis will be undertaken independently by two suitably experienced persons, led by CI [name] (expert in this area). Strategies to enhance trustworthiness of findings will include verbatim transcriptions of audio-recorded interviews and a clear audit trail (52).

## **Results, Outcomes and Future Plans**

This proposal was developed with carer input supported by Carers WA and the Consumer and Community Health Research Network, helping to ensure the appropriateness of the intervention and study processes. Consumer advocates continue to inform the study, which is grounded in robust preliminary work and designed to provide valid results to inform practice. As the study gets under way, we will appoint an advisory group that who can guide our external communication and dissemination plans. Important links will include with State and Federal Governments and others involved in health policy and planning, such as the WA Health Services Boards, primary care networks, etc. We will provide a 6 monthly newsletter on study progress to the study team, the participating hospitals, and other stakeholders identified as appropriate by the advisory group. To disseminate findings and ensure that those involved are aware of study closure, a final report will be produced, a media release will be circulated, and Carers WA and Qld will be asked to publish information about study closure and how to access findings on their website. Papers will be published in leading journals, and practitioner and consumer forums will be held in participating hospitals. Study participants will also be provided with a summary of study findings upon request. Dissemination strategies will all be logged. There is no anticipated secondary use of data at present but follow-up studies may be proposed, depending upon results.

**For carers in WA when the patient provides their own consent:**

WA site specific FECH Trial Carer PICF (including withdrawal form and summary)

DHS (now Services Australia) consent form

WA Carer Witnessed Verbal Consent Form (if unable to sign)

**For patients in WA able to provide their own consent:**

WA site specific FECH Trial Patient PICF (including withdrawal form and summary)

DHS (now Services Australia) consent form

WA Patient Witnessed Verbal Consent Form (if unable to sign)

**For carers in WA when the patient is included via a waiver of consent:**

WA site specific FECH Trial Carer PICF (including withdrawal form and summary)

DHS (now Services Australia) consent form

WA Carer Witnessed Verbal Consent Form (if unable to sign)

FECH Trial Opt Out Form and site specific WA Patient Information Sheet (including summary) - so that the patient may read the information sheet and summary and opt out if he or she regains capacity and wishes to do so.

**For carers in Qld when the patient provides their own consent:**

Qld FECH Trial Carer PICF (including withdrawal form and summary)

DHS (now Services Australia) consent form

Qld carer Witnessed Verbal Consent Form (if unable to sign)

**For patients in Qld able to provide their own consent:**

WA site specific FECH Trial Patient PICF (including withdrawal form and summary)

DHS (now Services Australia) consent form

WA Patient Witnessed Verbal Consent Form (if unable to sign)

**For carers in Qld when the patient is included via consent from a substitute decision maker:**

Qld FECH Trial Carer PICF (including withdrawal form and summary)

DHS (now Services Australia) consent form

Qld Carer Witnessed Verbal Consent Form (if unable to sign)

Site specific substitute decision maker for patient (SDM) PICF (includes form for SDM to withdraw the patient and summary)

DHS (now Services Australia) consent form for the patient if the carer has the authority to sign this on the patient's behalf (as specified on the form)

FECH Trial Opt Out Form and Qld Patient Information Sheet (includes summary) so that the patient may read the information sheet and opt out if he or she regains capacity and wishes to do so.

**For FECH Nurses:**

FECH Nurse PICF (including withdrawal form)
